#### Ascertainment of outcomes

##### Baseline data collection

The baseline questionnaire will include questions on socio-demographic and economic characteristics, bath time safety practices, bath time supervision and satisfaction with hot water supply. Families completing the baseline questionnaire will be offered an incentive (free bath mat or first aid kit) as incentives have been shown to increase response rates [22]. The design of the baseline questionnaire will be informed by individual face to face interviews with a sample of approximately 15 families residing in rented social housing. A purposive sample of families will be obtained to include families with differing maternal educational levels, different family composition, including children of differing ages, families with differing ethnic origins and differing levels of disadvantage. Interviews will take place in the families' homes and will explore issues surrounding bath safety and bath time supervision.

The first 50% of participants recruited to each arm will have their bath hot tap water temperature measured at recruitment to the trial. Water temperatures will be determined by direct measurement by a qualified plumber from City Building (Glasgow) Limited Liability Partnership, using a Type K thermocouple thermometer and rounded immersion probe. The temperature of the hot water supply will also be measured at an outlet other than a bath and without a TMV e.g. wash basin. This will enable detection of other methods to reduce hot water temperature such as reducing water heater thermostat settings.

#### Follow-up data collection

##### Primary outcome measure

A random sample of 15 families in each arm, who did not have their tap water temperature measured at baseline, will be chosen to have their tap water temperature measured at 3 months post fitting of TMVs and a separate random sample of 15 families in each arm will be selected to have their tap water temperature measured at 12 months post fitting of TMVs. Families will be offered a £10 voucher for use in local stores to increase response rates for water temperature measurements [22]. Measurements will be made in the same way as at baseline.

##### Secondary outcome measures

Secondary outcomes will be measured at 12 months post installation of TMVs (intervention arm) and at 12 months post randomisation (control arm). Data will be collected by questionnaire, which families can choose to complete by telephone or by post. The follow-up questionnaire will include questions on bath time safety practices, bath time supervision and satisfaction with hot water supply. Intervention arm families will also be asked questions about satisfaction with the TMV and the fitting process, attempts to adjust the TMV temperature setting, TMV problems, occupational details and work time lost as a result of TMV fitting or problems. TMV problems will also be ascertained from repair requests or complaints made to GHA by families. Families who complete the follow-up questionnaire will be offered a £5 gift voucher for use in local stores to increase response rates [22].

The design of the follow-up questionnaire will be informed by interviews with a sample of approximately 15 families in rented social housing who have had TMV valves fitted. A purposive sample of families will be obtained, as described above, but also, if possible, to include families with differing sites of installation of TMVs, and those who have experienced TMV failures. Interviews will be used to explore families' attitudes towards TMVs, experiences of using TMVs, attempts at altering temperature settings on TMVs and any changes in safety behaviour or bath time supervision following the fitting of TMVs. They will also be used to inform the development of questions on satisfaction with TMVs, bath time safety and supervision.

The cost-effectiveness analysis will be conducted from the perspective of public services and families. Costs associated with purchasing, fitting, maintaining, repairing and replacing TMVs will be estimated by GHA based on the unit cost of a TMV and associated pipe work plus the time required for plumbers to remove and re-fit the bath panel (or bath if necessary), to install the TMV and to test the bath hot tap water temperature before and after fitting the TMV. Participants' occupation, length of time off work and other costs incurred for TMV fitting or for repair or replacement in the event of TMV problems will be ascertained on the follow-up questionnaire and work time loss will be costed using relevant published wage rates. In addition, the costs associated with provision of the educational leaflet will be included in the cost profile of the intervention.

### Sample size

Ten families per arm are required to detect a reduction in the mean bath hot tap water temperature from 60.4 degrees Celsius (SD 9.1)[11] in the control group to 46 degrees Celsius in the intervention group, with 90% power and a 5% significance level (2 sided). Allowing 33% for losses to follow-up, 15 families in each arm will be randomly selected for tap water temperature testing at 3 and 12 months post valve installation (intervention arm) or randomisation (control arm). A different 15 families in each arm will be tested at 3 and 12 months.

For the secondary outcome measures, 50 families in each arm would provide:

• 80% power at the 5% significance level (1 sided) to test the hypothesis that the proportion of TMVs removed, disabled or whose temperature setting was adjusted did not exceed 6.5% if the true proportion of valves removed, disabled or adjusted was 1%.

• 80% power at the 5% significance level (2 sided) to detect a difference in the proportion of families agreeing that their bath hot tap water temperature was sufficiently hot from 90% in the control arm to 67% in the intervention arm.

To allow for losses to follow-up, a total of 120 participants will be recruited.

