### Analysis

The analysis will conform to a pre-specified analysis plan. Bath hot tap water temperatures will be described using the mean and standard deviation, or median and interquartile range, depending on the distribution of temperatures. The primary analysis will compare temperatures between treatment arms using an unpaired t-test to estimate the difference between the means and its 95% CI, assuming assumptions for undertaking these analyses are met. If assumptions are not met and no suitable transformation can be found, temperatures will be compared between treatment arms using the Mann-Whitney U test.

An intention to treat analysis will be undertaken replacing missing 3 and 12 month water temperatures (excluded participants and those where access could not be gained to homes for temperature measurement), with baseline temperatures, or where baseline temperatures are unavailable they will be replaced by the mean or median temperature for that treatment arm, dependent on the distribution of the temperatures.

The proportion of families with a bath hot water temperature ≤ 46 degrees Celsius will be compared between treatment arms using χ^2 ^tests and logistic regression to estimate the odds ratio and its 95% CI. Outcomes measured on an ordinal scale will be compared between treatment arms using χ^2 ^tests for trend, or will be dichotomised and analysed as binary variables depending on the distribution of responses.

Sensitivity analyses will be undertaken to examine the effect of adjusting for baseline temperature. Where baseline temperatures are unavailable they will be replaced by the mean or median temperature for that treatment arm, dependent on the distribution of the temperatures. These analyses will be undertaken using linear regression or a Mann-Whitney U test based on change scores.

The proportion of families in the intervention arm who have TMVs removed, replaced or repaired and who adjust the temperature setting of the TMV will be described using proportions and 95% CI.

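### Fifty valves give about 60% power, not the stated 80%, to show that the proportion removed, disabled or adjusted is no more than 6.5%

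*Protocol article*

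**What the plan says.** All the design figures are in the Sample size section of the protocol article. It gives two reasons for having 50 families per arm. The first is a one-sided 5% test, with stated power of 80%, whose purpose is "to test the hypothesis that the proportion of TMVs removed, disabled or whose temperature setting was adjusted did not exceed 6.5" per cent. The power is worked out for an assumed real rate of 1%. The second is 80% power, two-sided 5%, for 90% versus 67% of families finding their bath water hot enough.

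The recruitment target follows: "To allow for losses to follow-up, a total of 120 participants will be recruited". That is 60 per arm, so 50 is the number left after losses.

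The Analysis section describes the valve outcomes for "The proportion of families in the intervention arm who have TMVs removed, replaced or repaired and who adjust the temperature setting", using proportions and a 95% confidence interval. It names no interval method and does not mention the 6.5% limit. It refers to a pre-specified analysis plan, which is not at hand.

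**The concern.** The article gives every quantity needed to check this power: number of valves, level, sidedness, limit and true rate. When they are put together, the result is well below 80%. A separate analysis plan cannot cure this, because the figure is stated and not left out.

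Acceptability is the second objective, and the abstract says that the secondary outcomes, acceptability included, set the total of 120. A reader who trusts the figure would expect a four-in-five chance of showing that families rarely remove, disable or alter the valves. The real chance is nearer three in five. An inconclusive result might then be blamed on the valves when the cause is the sample size.

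**Working it through.** **Inputs** (protocol article, Sample size): n = 50 valves; one-sided level 5%; limit p0 = 0.065; true proportion p1 = 0.01; stated power 80%.

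**1. Can the stated 80% be reproduced?** The null hypothesis is p ≥ 0.065, rejected when few events occur. The normal formula with null and alternative variances gives

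n = [(1.645·√(0.065·0.935) + 0.842·√(0.01·0.99)) / 0.055]² = 79.1, so 80 valves.

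At n = 50 the same approximation gives power Φ[(0.055·√50 − 1.645·0.2465)/0.0995] = Φ(−0.17) = 43%.

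Other one-sided approximations at n = 50 give:
- null variance only: 47%
- continuity-corrected: 19%
- arcsine: 72%
- alternative variance only: 98.8%

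None is close to 80%. The one route that comes near exchanges the hypotheses (null 1%, alternative 6.5%):

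n = [(1.645·0.0995 + 0.842·0.2465)/0.055]² = 45.5, so 46, with 82% power at n = 50.

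That calculation tests whether the proportion is above 1%, not whether it is at most 6.5%. It may be where the figure came from, but the article gives no formula, so this is only an inference.

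**2. Exact calculation at n = 50.**
- Zero events: type I error 0.935^50 = 3.5%.
- At most one event: 0.935^50 + 50·0.065·0.935^49 = 15.5%, which is too large.

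Only zero events is a valid rule. Power at a true 1% is 0.99^50 = **60.5%**. Allowing one event would give 91.1% power, but at a 15.5% error rate. No count rule at n = 50 gives 80%.

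**3. Other numbers of valves, exact test.**

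| Valves | Rule | Type I error | Power at 1% |
|---|---|---|---|
| 44 | none (zero events gives 5.2%) | – | 0 |
| 45 | 0 events | 4.9% | 63.6% |
| 50 | 0 events | 3.5% | 60.5% |
| 60 | 0 events | 1.8% | 54.7% |
| 72 | at most 1 | 4.75% | 83.8% |

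Seventy-two is the smallest number with at least 80% exact power.

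**4. What the interval shows at 0/50.**
- One-sided 95% exact upper limit: 1 − 0.05^(1/50) = 5.8%. This is below 6.5% and agrees with the zero-event rule.
- Two-sided 95% upper limit: Clopper-Pearson 1 − 0.025^(1/50) = 7.1%; Wilson 3.84/(50 + 3.84) = 7.1%; Agresti-Coull 8.5%; mid-P 5.8%; Jeffreys 4.9%.

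**5. The limit that 50 valves can support.** With one event in 50 the one-sided exact 95% upper limit is 9.1%. At most one event has probability 91.1% at a true 1%.

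**6. The other secondary power claim.** For 90% versus 67% with 50 per arm, the pooled proportion is 0.785 and power is Φ[(0.23·√50 − 1.96·√(2·0.785·0.215))/√(0.09 + 0.2211)] = Φ(0.87) = 81%. The stated 80% is right.

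**The case against.** One defence is that exact tests are conservative and the planners may have meant another test. This does not rescue the figure. At n = 50 the null-variance z-test gives p = 0.031 at zero events and 0.098 at one; the mid-P values are 0.017 and 0.095. Both also reject only at zero events, so their true power is the same 60.5%.

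A fairer defence is that this is a single-arm secondary outcome, set beside a correctly powered comparison on the same 50 per arm. That stands, and it limits the weight of the point.

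Four stronger readings are tempting, but the document does not support them.

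- *Even a perfect result would fail.* This holds for a two-sided 95% Clopper-Pearson, Wilson or Agresti-Coull interval at 0/50, but not for mid-P or Jeffreys. With 0/60 the Clopper-Pearson limit is 6.0%. The Analysis section names no method and does not make the interval a decision rule. The one-sided test in the Sample size section does succeed at 0/50.
- *A different set of events is analysed.* The Analysis section covers removal and adjustment. Only disabling is not named, while repair and replacement are added.
- *Fewer than 50 valves always makes it worse.* Exact power rises slightly, to 63.6% at 45, and falls to zero only below 45.
- *The loss allowances contradict each other.* Going from 60 to 50 per arm allows 16.7%, while the temperature outcome has "Allowing 33% for losses to follow-up". That 33% is stated for home temperature visits. The valve and satisfaction outcomes come from a telephone or postal questionnaire, and valve problems also from the housing association's records. Loss rates may differ, so 33% here is a scenario and not an inconsistency.

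That the article describes no test against 6.5% is not a finding either, since the analysis plan may hold it.

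**Conclusion.** The stated 80% is wrong for the test as worded. The power is 60.5% at 50 valves, about 20 points lower, and 54.7% if all 60 families are followed. Eighty per cent needs 72 valves by the exact test or 80 by the normal formula. This rests only on the article's own inputs and on independent valves sharing one event rate.

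A smaller, conditional point goes with it. A two-sided 95% interval is not the counterpart of a one-sided 5% test. If it were computed by Clopper-Pearson or Wilson, the two could disagree at 0/50 (7.1% against 5.8%). It should not be read as saying that the planned analysis must fail.

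The error is confined to one secondary outcome. The primary outcome and the 90% versus 67% comparison are unaffected.

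**What to change.** In the Sample size section, restate the power as about 60% for the 6.5% limit with 50 valves. Alternatively, state the limit that 50 valves can support: at most one event gives a one-sided exact 95% upper limit of 9.1%. That is a less favourable figure. Nothing in the document shows that it would be an acceptable rate, so the sponsor would have to justify it.

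In the Analysis section, or in the analysis plan, report the composite that was sized (removed, disabled or adjusted) with an exact one-sided 95% upper limit, which is the upper end of a two-sided 90% exact interval. Repairs and replacements can still be described separately.

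The cost is a few sentences and a less favourable stated power. No further families are needed unless the sponsor wants to keep both the 6.5% limit and 80% power. In that case at least 72 evaluable valves are required.

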### Randomisation

After giving informed consent, families will be randomised to treatment arms. The randomisation schedule will be generated by the trial statistician using a computerised random-number generator in Stata [23], using a permuted block design with a random block size. Equal numbers will be allocated to the two groups. No stratification will be used. Group allocations will be placed in sequentially numbered, opaque, sealed envelopes. These will be opened sequentially by a researcher independent of the research team after participants have consented. The independent researcher will inform the study research fellow of the allocation who will inform GHA of the allocation. The research fellow will write to each family informing them of the allocation and provide details of how they will be contacted by GHA to organise water temperature measurement and TMV fitting.

### Blinding

It is not possible to blind participants, plumbers or researchers to treatment group allocation. Data will be analysed blind to treatment group allocation.

### Withdrawals

Participants will be free to withdraw from the trial at any stage. Those who move from the property before follow-up will be withdrawn from the trial.

### Analysis

The analysis will conform to a pre-specified analysis plan. Bath hot tap water temperatures will be described using the mean and standard deviation, or median and interquartile range, depending on the distribution of temperatures. The primary analysis will compare temperatures between treatment arms using an unpaired t-test to estimate the difference between the means and its 95% CI, assuming assumptions for undertaking these analyses are met. If assumptions are not met and no suitable transformation can be found, temperatures will be compared between treatment arms using the Mann-Whitney U test.

An intention to treat analysis will be undertaken replacing missing 3 and 12 month water temperatures (excluded participants and those where access could not be gained to homes for temperature measurement), with baseline temperatures, or where baseline temperatures are unavailable they will be replaced by the mean or median temperature for that treatment arm, dependent on the distribution of the temperatures.

The proportion of families with a bath hot water temperature ≤ 46 degrees Celsius will be compared between treatment arms using χ^2 ^tests and logistic regression to estimate the odds ratio and its 95% CI. Outcomes measured on an ordinal scale will be compared between treatment arms using χ^2 ^tests for trend, or will be dichotomised and analysed as binary variables depending on the distribution of responses.

Sensitivity analyses will be undertaken to examine the effect of adjusting for baseline temperature. Where baseline temperatures are unavailable they will be replaced by the mean or median temperature for that treatment arm, dependent on the distribution of the temperatures. These analyses will be undertaken using linear regression or a Mann-Whitney U test based on change scores.

The proportion of families in the intervention arm who have TMVs removed, replaced or repaired and who adjust the temperature setting of the TMV will be described using proportions and 95% CI.

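### The intention-to-treat rule fills missing bath temperatures with an arm-level constant analysed as data, which distorts either the confidence interval or the effect size, depending on an unstated time point

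*Protocol article*

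**What the plan says.** The Analysis section of the protocol article names an unpaired t-test as the primary comparison of temperatures. It then describes an intention-to-treat analysis in which a missing 3- or 12-month temperature takes the family's baseline value, "or where baseline temperatures are unavailable they will be replaced by the mean or median temperature for that treatment arm". The missing cases it names are excluded participants and homes that could not be entered for measurement. It gives no time point for the arm mean or median, and it does not say whether this analysis is the primary t-test or runs beside it.

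Under Follow-up data collection, the 3-month sample is 15 families per arm "who did not have their tap water temperature measured at baseline". The 12-month sample is a separate 15 per arm, and the restriction is not repeated. Under Baseline data collection, the first half of recruits in each arm have a baseline reading.

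The Sample size section starts from "Ten families per arm are required to detect a reduction in the mean bath hot tap water temperature" and continues: "Allowing 33% for losses to follow-up, 15 families in each arm will be randomly selected for tap water temperature testing".

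**The concern.** The rule and the sampling plan collide. The rule prefers the family's own baseline, but the 3-month sample is chosen so that no baseline exists. The fallback thus becomes the working rule.

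A fallback constant adds no information. If it is the observed follow-up mean of the arm, it leaves the sum of squares unchanged while raising the nominal sample size, so the standard error is understated. It also gives any unmeasured intervention home without a valve the mean of the homes that were measured, which defeats the purpose of an intention-to-treat analysis. If the constant is instead a baseline mean, a fitted but unmeasured home is entered as though it had no valve.

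At stake are the interval and the effect size of the intention-to-treat comparison, in a trial meant to inform housing policy.

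**Working it through.** **Inputs.** Sample size section: "reduction in the mean bath hot tap water temperature from 60.4 degrees Celsius (SD 9.1)[11] in the control group to 46 degrees Celsius", so the difference is 60.4 − 46 = 14.4 °C with SD 9.1; two-sided 5% level, 90% power; 10 evaluable and 15 selected per arm. Randomisation section: "Equal numbers will be allocated to the two groups". Total recruitment is 120, so 60 per arm.

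**The plan's own figure.** With the noncentral t distribution, 9 per arm gives 88.3% power and 10 per arm gives 91.7%, so n = 10. Allowing for loss, 10/(1 − 0.33) = 14.9, rounded up to 15. Both stated figures reproduce.

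**Is a baseline available?** At 3 months, no; the text says so. At 12 months it is an inference: 60 per arm, of whom 30 have a baseline, leaves 30 = 15 + 15. Two non-overlapping samples of 15 use up exactly the families without a baseline.

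**Reading A: the fill is the arm's own follow-up mean.** Let o be the number observed of 15, and SS the sum of squares in an arm. Filling leaves SS unchanged.

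- Correct variance of an arm mean: SS/[(o − 1)·o]. Variance as analysed: SS/(14·15).
- Ratio of standard errors: √[o(o − 1)/(14·15)]. For o = 10: √(90/210) = 0.655, so 34.5% too small.
- In SD units, the standard error of the difference is √(2/10) = 0.447 on measured values and 0.447 × 0.655 = 0.293 after filling.
- True type I error: 2·P(t₁₈ > 2.048 × 0.655) = 19.7%. Simulation with 200,000 replicates gives 19.5%, or 20.2% with a median fill.
- Simulated coverage of the nominal 95% interval: 80% with equal SDs, 79% if the intervention SD is 2 (an assumed value).

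| Filled per arm, of 15 | SE ratio | Type I error |
|---|---|---|
| 1 | 0.931 | 6.8% |
| 2 | 0.862 | 9.0% |
| 3 | 0.793 | 11.9% |
| 4 | 0.724 | 15.4% |
| 5 | 0.655 | 19.7% |

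With 5 filled in one arm and 2 in the other, type I error is 13.8%.

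*Bias under reading A (illustration).* Suppose all 5 missing intervention homes had no valve and ran at 60.4 °C, and fitted homes averaged 46 °C. The true intention-to-treat difference is 14.4 × 10/15 = 9.6 °C. The rule reports 14.4 °C.

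**Reading B: the fill is the arm's baseline mean (30 homes per arm).** With 5 filled per arm, simulated type I error is 5.8%. If the 5 missing intervention homes were in fact fitted, the true effect is 14.4 °C but the expected estimate is 14.4 × 10/15 = 9.6 °C. The simulated 95% interval then covers 14.4 °C about 72% of the time, and power is 86%.

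**Does the conclusion of the test change?** At the planned effect, rejection is 91.7% on 10 measured per arm and 98.5% with the reading A fill. Rejection is likely either way.

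**The case against.** The strongest reply is that the text does not fix reading A. The sensitivity paragraph of the same section uses almost the same words for what can only be a baseline fill. If that meaning carries over, the 20% figure disappears, and unmeasured intervention homes are filled hot rather than credited with a valve. If those homes were indeed unfitted, the estimate would then be about right. This stands, and it is why the size of the problem is given for each reading. It does not rescue the rule: the same fill is wrong by 14.4 − 9.6 = 4.8 °C when the missing homes were fitted.

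Second, the 12-month sample might include families with a baseline reading. If it were drawn from the remaining 45 per arm, 30 of those would have one, and type I error under reading A would be about 8% (assuming a correlation of 0.3 to 0.8 between baseline and follow-up). This also stands; the claim that every fill is a constant is secure only for 3 months.

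Three stronger inferences are tempting but not supported:

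- *That the primary p-value and interval are invalid.* The protocol describes the t-test first and the intention-to-treat analysis separately, and does not say that one replaces the other.
- *That the missing intervention homes are largely unfitted.* Unsuitable pipe work is an exclusion, and the Discussion expects trouble gaining access for fitting. But families also move house, and failed access for measurement does not mean that no valve was fitted. The 9.6 against 14.4 °C contrast is an illustration, not an expectation. A measured home without a valve keeps its own value.
- *That fills become certain successes at 46 °C or below in one arm and failures in the other.* The protocol does not say that filled values enter that outcome, and the planning mean for the intervention arm is exactly 46 °C. If fitted homes ran at 44 °C, 2 unfitted among 10 measured would give (8 × 44 + 2 × 60.4)/10 = 47.3 °C, and the fills would count as failures.

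**Conclusion.** The point holds, with its size conditional on the reading. The protocol itself fixes a rule that at 3 months, and probably at 12, puts an arm-level constant in place of every missing temperature and analyses it as observed.

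Under the follow-up-mean reading, with the planned 33% loss in both arms, the standard error is about 35% too small, type I error about 20% and coverage about 80%; with 2 or 3 of 15 missing, type I error is still 9% to 12%. Under the baseline-mean reading, the test is close to nominal but a real 14.4 °C effect falls to about 9.6 °C if the missing homes were fitted. These figures assume normal temperatures with the protocol's SD of 9.1 in both arms unless stated otherwise.

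A reader might infer a serious risk of a false-positive trial. The documents do not support that: the planned effect is large enough for the null to be rejected with or without the fill. The damage is to the interval and effect size of the intention-to-treat analysis.

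**What to change.** - Delete the arm mean or median replacement.
- State that the primary analysis is the t-test on all selected families with a measured temperature, in the arm randomised whether or not a valve was fitted, with n equal to the number measured.
- State that filled values do not enter the outcome of 46 °C or below.
- Add one sensitivity analysis that draws unmeasured intervention homes from the observed control-arm distribution, by proper multiple imputation so that the variance is not understated. Keep this as a stress test, not the main analysis: about 10 values per arm are a thin base for imputation, and the second-outlet temperature is taken on the same visit, so it is missing when access fails.

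The cost is a change of wording and a little code. Planned power is kept, since 10 measured per arm gives 91.7%. The downside is a wider interval: at 33% loss the standard error is 1/0.655 = 1.53 times that under the follow-up-mean fill, so the interval is roughly one and a half times as wide.

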### Objectives

The objectives of this research are to:

1. assess the effectiveness and cost effectiveness of TMVs in reducing bath hot tap water temperature in the homes of families with pre-school children living in rented social housing

2. assess the acceptability of TMVs to families with pre-school children living in rented social housing

3. assess the impact on bath time safety practices (i.e. adverse and potentially adverse effects from fitting TMVs, such as use of less safe methods of obtaining hotter bath water, reduced supervision or omitting to check water temperature on the assumption that it is safe)

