### Participants

Families with pre-school children living in Glasgow Housing Association (GHA) housing. Families will be excluded if they are not GHA tenants, if their bathroom pipe work is found to be unsuitable for fitting a TMV or if they are already participating in on-going tap water scald prevention studies.

A range of recruitment strategies will be used. These will include:

(a) written invitation from GHA to (i) GHA tenants on the East End Child Safety Project (EECSP) Database, which is a database of families who have taken part in a previous child safety project and (ii) to tenants aged 18 to 40 years identified from the GHA tenant database.

(b) face-face contact with (i) local housing organisations (LHOs) who will provide information about the study to families due to have kitchen or bathroom refurbishments or other repairs which necessitate the LHO to visit the family's home and to families at open days and other events, and (ii) local projects or organisations such as the EECSP and the Parents and Children Together (PACT) team will provide information about the study to GHA tenants they meet during project activities

(c) articles describing the study will be placed in LHO newsletters and local newspapers and GHA tenants who would like to know more about the study will be asked to contact the research team.

Families expressing interest in participating will be contacted by the research team to discuss the study, answer any questions and assess eligibility. Those agreeing to participate will be asked to complete a baseline questionnaire, which families can choose to complete by telephone or by post.

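### The stated between-arm analysis of bath-time practices and hot-water satisfaction has no baseline term, although the same topics are asked at baseline; adjusting would gain some precision at little cost

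*Protocol article*

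**What the plan says.** Under Participants, the protocol article says "Those agreeing to participate will be asked to complete a baseline questionnaire", so the baseline questionnaire is meant for every family. Under Baseline data collection it covers, besides socio-demographic items, "bath time safety practices, bath time supervision and satisfaction with hot water supply". Under Secondary outcome measures (follow-up) the article says "The follow-up questionnaire will include questions on bath time safety practices, bath time supervision and satisfaction with hot water supply", and these outcomes are taken at 12 months.

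Objective 3 concerns unintended effects of the valve on safety practices, among them "reduced supervision or omitting to check water temperature on the assumption that it is safe". The Risks section points to these same secondary outcomes as the way such effects are measured.

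Under Analysis: "Outcomes measured on an ordinal scale will be compared between treatment arms using" chi-squared tests for trend, or such outcomes "will be dichotomised and analysed as binary variables depending on the distribution of responses". Neither route mentions the baseline questionnaire answer. The one baseline adjustment named is for water temperature, as a sensitivity analysis, and temperature is measured at baseline only in the first half of each arm. The section also refers to a pre-specified analysis plan, which is not shown.

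**The concern.** The article goes beyond leaving the method open: it names one. A chi-squared test for trend takes no covariate and returns a p-value without an effect estimate. The only adjustment stated is for the variable known at baseline in half the families. For the questionnaire topics, which every participating family is asked about at baseline, none is stated.

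Habits such as checking the water or staying with the child are likely to persist within a family, so the baseline answer should explain part of the spread at 12 months. The arms are small (about 50 families each after losses) and randomisation is unstratified. Leaving the baseline answer out then makes the estimate less precise than the collected data may allow. This matters most for objective 3, the only harm pathway the article describes, for which no power is stated.

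**Working it through.** **1. The plan's own figure.** The Sample size section gives 50 families per arm for satisfaction, 90% v 67%, two-sided 5%, 80% power. With mean proportion 0.785 and no continuity correction:

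n = [1.96·√(2·0.785·0.215) + 0.842·√(0.90·0.10 + 0.67·0.33)]² / 0.23²
= [1.96·0.581 + 0.842·0.558]² / 0.0529 = 48.9, so 49 per arm.

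Power at 50 per arm is 80.9%. The figure reproduces without any baseline information. It is somewhat method-dependent: 58 per arm with a continuity correction, and 75.7% power at 50 per arm by Fisher's exact test.

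**2. A safety practice, unadjusted.** The article gives no rates. Assume a practice present in 80% of controls and 57% of intervention families, the same 23-point difference as in the satisfaction design. Mean proportion 0.685, 50 per arm:

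z = [0.23·√50 − 1.96·√(2·0.685·0.315)] / √(0.80·0.20 + 0.57·0.43)
= [1.626 − 1.288] / 0.636 = 0.53, so power is about 70%.

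**3. The same practice, adjusted.** Baseline and 12-month answers are simulated from correlated latent normals, with 80% at baseline. A logistic regression on arm and baseline answer is fitted:

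| Latent correlation (assumed) | Power, unadjusted | Power, adjusted |
|---|---|---|
| 0.30 | about 70% | 73% |
| 0.50 | about 70% | 74% |
| 0.70 | about 70% | 82% |
| 0.85 | about 70% | 89% |

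Rejection under no effect was about 5–7%. A repeat run agreed to within about two points when arm was tested by likelihood ratio. A Wald test gained less, most visibly at the highest correlation.

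**4. On the risk-difference scale.** A linear model with robust errors, same rates, gives these standard errors of the difference:

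| Latent correlation | Correlation of the yes/no answers (phi) | SE unadjusted → adjusted | Reduction |
|---|---|---|---|
| 0.50 | 0.30 | 0.091 → 0.088 | 3% |
| 0.70 | 0.45 | 0.091 → 0.083 | 9% |
| 0.85 | 0.61 | 0.091 → 0.076 | 16% |

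**5. Rough gain for the satisfaction design.** The variance factor 1 − ρ² is 0.96, 0.91, 0.75 and 0.51 for ρ = 0.2, 0.3, 0.5 and 0.7. Power at 50 per arm goes from 80.9% to 82.5%, 84.5%, 90.7% and 97.9%. The factor is borrowed from continuous outcomes and is optimistic: at phi 0.61 it implies a standard error cut of 1 − √(1 − 0.61²) = 21%, against 16% simulated.

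**6. Why not a change score.** Its variance factor is 2(1 − ρ): 1.6 at ρ = 0.2, 1.0 at 0.5, 0.6 at 0.7. Below ρ = 0.5 it is worse than the 12-month answer alone. Covariate adjustment does not carry that penalty.

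**7. Chance imbalance.** For a practice at 80% at baseline, the standard deviation of the difference between arms is √(2·0.8·0.2/50) = 8 points. A gap of 10 points or more is 1.25 standard deviations and arises in about 21% of trials. At phi 0.45 about 0.45·10 = 4.5 points would carry into the 12-month difference.

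**The case against.** The strongest reply is that this is ordinary analysis-plan detail. The article is condensed, it refers to a plan that is not shown, and adjustment of secondary outcomes may be set out there. The dichotomised route could take a covariate, since logistic regression is already named for the outcome of 46 degrees or below. This stands in part: the plan may already contain the adjustment. But the trend test is a stated choice that cannot carry a covariate, so the text as it reads can be improved.

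A reader might go further and infer that the trial discards its baseline answers, or that it needs them to see an effect on behaviour. The documents support neither. Nothing says the answers go unused. Because families are randomised, the difference between arms at 12 months already estimates the valve's effect on practices. Children growing older affects both arms alike, and families who never checked the water are balanced in expectation. Nor does chance imbalance produce excess false signals, because the unadjusted test's error rate already allows for it.

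Three further limits stand. Every correlation, and the 80% v 57%, is assumed, and at the low end the gain is slight. The two questionnaires share topics, but each is informed by its own set of interviews, so identical items are not assured. Satisfaction with the valve is collected only in the intervention arm and has no baseline counterpart.

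The objection that a gain seen in a linear model need not hold for a logistic one does not stand, since power also rose when the logistic model itself was simulated.

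**Conclusion.** The point holds as one of efficiency. The stated comparisons of safety practices, supervision and hot-water satisfaction leave out the family's baseline answer, and the trend test cannot include it. The comparisons remain valid and unbiased, and the satisfaction comparison meets its stated power without baseline.

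For an assumed 80% v 57% with 50 per arm, adjustment lifts power from about 70% to 73–89%. The lower figures apply if answers are only weakly related over the year. The result rests on three assumptions: the correlation, on which the article gives nothing; the existence of matching items; and completion of the baseline questionnaire before the family learns its allocation, which the recruitment sequence suggests but does not state.

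**What to change.** For each practice, supervision and hot-water-satisfaction outcome with a matching baseline item:

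- Make the between-arm estimate a logistic regression (binary) or proportional-odds regression (ordinal) on arm, with the family's own baseline answer as covariate, and report it with a 95% CI.
- Preferably also report a standardised risk difference, because the adjusted odds ratio is conditional on baseline and is not the same quantity as the unadjusted one.
- Prefer the likelihood-ratio test for arm at this sample size.
- Keep the chi-squared trend test as supporting.
- Keep families lacking a baseline answer in the model through a missing-category indicator.

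Where there is no matching item, as for satisfaction with the valve, keep the stated analysis. The proportion who stopped a safe practice among those reporting it at baseline may be added by arm, as a descriptive figure. With 80% at baseline (assumed) that is about 0.8·50 = 40 families per arm.

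The cost is a change of wording in the analysis plan, provided the two questionnaires use the same items. If the follow-up questionnaire is not yet final, repeating the baseline wording for these items would secure that.
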